### 3. BACKGROUND INFORMATION

#### 3.1 NK T cell Lymphomas

Nasal natural killer (NK)/T-cell lymphoma is a unique type of non-Hodgkin lymphoma (NHL) that is almost always associated with Epstein-Barr virus (EBV) and shows a geographic predilection for Asian and South American populations[1]. Extranodal NK/T cell lymphoma (NKTCL), nasal type, is a distinct subtype of lymphoma which predominantly occurs in extranodal sites including nasal/paranasal area, and less frequently in skin, gastrointestinal tract and other organs [2]. In patients with disease stage III-IV, the 5-year overall survival (OS) rate is 50% [3].

Aberrant glutamine metabolism is involved in the pathogenesis of NKTCL.

Asparaginase exerts an anti-metabolic effect by depleting extracellular asparagine and inhibiting glutamine-dependent tumor cell growth[4]. Asparaginase-containing chemotherapy achieves high efficacy in patients with NKTCL[5]. First-line intensive chemotherapy like SMILE (dexamethasone, methotrexate, ifosfamide, asparaginase, and etoposide) has a complete response (CR) rate of 40% (8/20) in advanced stage NKTCL, which should be safely administered with careful attention to adverse effects (AEs) [6].

Tumor immune escape is an emerging hallmark of cancer and an important target for cancer therapy. Programmed cell death receptor 1 (PD-1) and PD ligand 1 (PD-L1) are important immune checkpoint molecules involved in T cell-mediated immune response and are key regulators of tumor immune escape[7, 8]. PD-L1, also known as B7-H1, is an immunomodulatory cell-surface glycoprotein and a member of the B7 family of costimulatory molecules that is primarily expressed by antigen-presenting cells and serves to regulate the cellular immune response. Binding of PD-L1 to its cognate receptor PD-1 inhibits proliferation of activated T cells in peripheral tissues leading to “T-cell exhaustion”, a functional phenotype that can be reversed by PD-1 blockade[9]. Aberrant expression of PD-1/PD-L1 on tumor cells or tumor-infiltrating lymphocytes has conferred adverse prognostic impact in multiple solid and hematopoietic malignancies[10]. Blockade of the PD-1/PD-L1 interactions with monoclonal antibodies has achieved encouraging efficacy and has been approved by the US Food and Drug Administration (FDA) in many malignancies including Hodgkin lymphoma (HL) and primary mediastinal large B-cell lymphoma (PMBL)[20]. In HL and PMBL, the gene amplification of the 9p24.1 locus (PD-1 ligands and JAK2) promotes PD-L1 expression via the JAK2-STAT signaling pathway in a dose-dependent manner[11]. In EBV-associated lymphoma, latent membrane protein 1 (LMP1) promotes AP1 and JAK-STAT signaling and promotes PD-L1 expression via an AP-1-dependent enhancer[12]; blockade of PD-1/PD-L1 interactions successfully inhibited EBV-induced lymphoma growth in a mouse model[13].

Expression of PD-L1 on tumor cells has been reported in patients with NKTCL[9], however, the role of PD-1/PD-L1 in the pathogenesis of NKTCL remains poorly understood.

There is a close correlation between Epstein–Barr virus (EBV) infection, PD-L1 expression and NKTCL. Almost all cases of NKTCL exhibited a positive result of EBV-encoded RNA (EBER) in situ hybridization in tumor samples. Additionally, pre- and post-treatment levels of circulating EBV DNA had significant prognostic implications for NKTCL patients[14-17].

NKTCL cells express programmed death protein ligand 1 (PDL1) and the EBV latent membrane protein 1 (LMP1) upregulates PDL1 expression through the MAPK/NF- $\kappa$ B pathway. Ligation of PD1 on effector T-cells with PDL1 on lymphoma cells leads to inhibition of T-cell activity, providing a potential mechanism for NK/T-cell lymphoma cells to evade immunosurveillance.

Pembrolizumab, a humanized anti-PD-1 monoclonal antibody, has revealed to be highly effective for relapsed/refractory ENKL failing L-asparaginase-containing therapy. In a recent study seven patients with relapsed NK/T-cell lymphoma failing previous L-asparaginase regimens (N=7) and allogeneic haematopoietic stem cell transplantation (HSCT) (N=2) were treated with the anti-PD1 antibody pembrolizumab and all seven patients responded, with five complete and two partial responses. In the partial responses, weaker staining for PDL1 expression was found in ~20% of cells in one of patients[18]. Nivolumab, another fully humanized anti-PD-1 monoclonal antibody, has later proven to be effective in ENKL. Three relapsed ENKL patients were treated with 80 to 360 mg of nivolumab. Two attained complete response, and the remaining one a partial response[19]. These findings suggest that checkpoint inhibitors are strongly promising for the treatment of ENKL.

Sintilimab, another fully humanized anti-PD-1 antibody with increased affinity to PD-1 than that of pembrolizumab, is implicated in the treatment of NKTCL, HL and solid tumors[20].

Our aim is to conduct a clinical trial to evaluate the activity and tolerability of the anti PD1 agent sintilimab in combination with pegaspargase for the initial treatment of previously untreated patients with advanced stage NKTCL.

This is a preparatory study for a larger future randomized study.

## **4. STUDY OBJECTIVES**

The aim of the study is to test the hypothesis that the combination of sintilimab and pegaspargase might be an active and safe therapeutic option in patient with advanced stage NKTCL.

### **4.1 Primary Objective**

The primary objective is to test the efficacy of sintilimab and pegaspargase in patients with advanced stage NKTCL.

### **4.2 Secondary Objectives**

To further explore the efficacy and safety of sintilimab and pegaspargase as initial treatment of patients with advanced stage NKTCL.

## **5 STUDY OUTCOMES**

### **5.1 Primary Outcome**

The primary objective will be calculated using CRR at the end of cycle 6 (defined according to 2014 Lugano criteria and 2016 Refinement of the Lugano Classification lymphoma response criteria in the era of immunomodulatory therapy)

### **5.2 Secondary Outcomes**

- ORR at the end of cycle 6 (defined according to 2014 Lugano criteria and 2016 Refinement of the Lugano Classification lymphoma response criteria in the era of immunomodulatory therapy)
- 2-year progression free survival
- 2-year overall survival
- Duration of response
- EBV-DNA load change
- Rate of adverse events coded according to CTCAE ver 4.0
- QoL
- Treatment-related mortality

## 6. STUDY DESIGN AND STUDY POPULATION

### 6.1 General Study Design

This phase II, open-label, single arm trial will evaluate the efficacy and safety of anti-PD-1 antibody in combination with pegaspargase in treatment of newly diagnosed advanced stage NK/T-cell lymphoma.

All eligible patients will receive induction treatment for six cycles of Anti-PD-1 antibody sintilimab plus pegaspargase (21-day cycle) and sintilimab monotherapy maintenance treatment for about 2 years (21-day cycle).

The follow-up period will last up to 2 years from the date of last subject enrollment.

#### Response assessment

Response will be evaluated according to 2014 Lugano criteria and 2016 Refinement of the Lugano Classification lymphoma response criteria in the era of immunomodulatory therapy using CT scan and PET-CT scan.

Patients will be evaluated for safety and tolerability of study treatment.

Anti-tumor activity assessment will be performed at cycle 3 and 6, every 4 months in the first year of follow-up, followed by every 6 months in the second year of follow-up (end of study).

For patients who experience PD or who discontinue the study due to an adverse event (AE) or a serious adverse event (SAE), the full assessment (EOT) should be obtained 30 days of the last dose of study treatment or before another anticancer therapy is initiated, whichever is shorter.

**Figure 1– Study Flowchart**

[figure not shown]

## 6.2 Eligibility Criteria

### 6.2.1 Inclusion Criteria

To be eligible for inclusion, each patient must fulfil all of the following criteria:

1. Coconfirmed histological diagnosis of NKTCL nasal type
2. No previous anti-lymphoma treatment
3. Age > 18 years
4. Ann Arbor stage III-IV
5. At least one measurable/evaluable site after diagnostic biopsy before treatment start
6. ECOG performance status of 0-2
7. Adequate hematological and organ function; i.e.  
ANC >1000 cells /mmc, platelet counts > 50.000/mmc, Hemoglobin > 9 g/dl  
AST, ALT <3 x ULN; serum bilitubin < 1.5x ULN (patient with Gilbert disease can be enrolled)  
Serum creatinine < 2 x ULN or creatinine clearance > 50ml/min
8. Tumor tissue (fresh preferred, archival tissue is also acceptable)
9. For women of childebearing potential a negative pregnancy test on day 1 of cycle 1 and agree to adopta adequate measure to avoid pregnancy during study treatment and for at least one year from EOT.
10. For men agreement to remain abstinent or to use barrier contraception
11. Signed Informed consent

### 6.2.2 Exclusion Criteria

Patients who fulfill any of the following criteria will be excluded:

1. Confirmed histological diagnosis of aggressive NK cell leukemia
2. Early stage disease (AA stage I-II)
3. Evidence of suspect of CNS disease.
4. Has an active autoimmune disease that has required systemic treatment in past 2-years (ie, with use of disease modifying agents, corticosteroids or immunosuppressive drugs), including but not limited to myatonia gravis, myositis, autoimmune hepatitis, systemic lupus erythematosus, rheumatoid arthritis, inflammatory bowel disease, vascular thrombosis associate with antiphospholipid syndrome, wegenger's granulomatosis, Sjogren syndrome, guillan barreè syndrome, multiple sclerosis, vasculitis or glomerulonephritis. The following exception are allowed: patients with autoimmune related hyopthiroidism or type I diabetes mellitus who are on stable treatment. Replacement therapy (eg, thyroxine, insulin, or physiologic corticosteroid replacement therapy for adrenal or pituitary insufficiency) is not considered a form of systemic treatment and is allowed.
5. Treatment with systemic immunosuppressive medications, including prednisone, cyclophosphamide, azathioprine, methotrexate, thalidomide and anti tumor necrosis factor (anti-TNF) agents within 2 weeks prior to cycle 1 day 1; inhaled corticosteroids are allowed.

6. Active infection requiring systemic therapy
7. History of (non-infectious) pneumonitis that required steroids; evidence of interstitial lung disease or active, non-infectious pneumonitis
8. Significant cardiovascular disease, myocardial infarction in the previous 3 months, unstable arrhythmias, or unstable angina.
9. History of other(s) infiltrating cancer(s) in the previous 3 years that were not treated with curative intent or who are still receiving anticancer therapy (including hormone therapy for breast or prostate cancer).
10. HBsAg, HCV or HIV positivity. Positive serology is admitted for HBV and HCV but DNA/RNA test must be negative
11. Prior therapy with an anti-PD-1, anti-PD-L1, or anti-PD-L2 agent
12. Pregnant or lactating women
13. Administration of a live attenuated vaccine within 4 weeks before cycle 1 day 1. Patients must not receive live, attenuate vaccines, including influenza vaccines at any time during study.
14. Other uncontrollable medical condition that may that may interfere the participation of the study

### **6.2.3 Criteria for Withdrawal / Discontinuation of Participants**

Patients might have continued with therapy unless any of the following occurs:

1. Progressive disease;
2. Unacceptable toxicity dictating cessation of treatment;
3. Any change in medical status of the patient (including pregnancy) such that the Investigator believed that patient safety was compromised or that it was in the best interest of the patient to stop treatment;
4. Withdrawal of consent (included patients deciding to discontinue completely his/her study participation for any reason and refusing the Sponsor any authorization to collect information about his/her disease status: in this case no further evaluation was to be performed and no attempts were to be made to collect additional data);
5. Patient's refusal to continue the study treatment (included patients deciding to discontinue completely his/her study participation for any reason but accepting to be followed up by the Sponsor for the collection of information regarding his/her disease status);
6. Non-compliance by the patient with protocol requirements;
7. Patient lost to follow-up. If a patient did not return for scheduled visits, every effort was to be made to re-establish contact. In any circumstance, every effort was to be made to document patient outcome;

## **7. STUDY INTERVENTION**

### **7.1 Induction phase**

Pegaspargase 2500IU/ m2 administered by intramuscular injection on Day 1 of each 21-day cycle for 6 cycles.

Sintilimab 200mg administered intravenously on Day 2 of each 21-day cycle for 6 cycles.

### **7.2 Maintenance phase**

Sintilimab 200mg administered intravenously on Day 1 of each 21-day cycle for up to 28 cycles in maintenance treatment.

### **7.3 Prophylaxis for CNS relapse and Radiation**

Patients with involvement of bone marrow, nasal or paranasal sinuses, orbit, breast, kidney, adrenal gland, or testis received prophylactic intrathecal methotrexate 10mg and cytarabine 50mg for 4 cycles during induction treatment.

For patients with limited lesions or residual disease at the end of induction treatment, radiation is recommended upon Investigators' consideration.

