### **Permitted medications**

Oral contraceptives, hormone replacement therapies, or other maintenance therapy are allowed to continue

Use of inhaled corticosteroids and mineralocorticoids is allowed

Megestrol administered as an appetite stimulant is acceptable

Prophylaxis of nausea and vomiting is allowed as per institutional practice

Use of antimicrobial and/or anti viral prophylaxis according to institutional guidelines is allowed. This also include the use of medications to prevent hepatitis B reactivation.

Flu vaccination should be given during flu season but live attenuated vaccines must be avoided.

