### **Prohibited medications**

Patients should not receive long term treatment with corticosteroids other than intermittent corticosteroids for prophylaxis or for treatment of autoimmune conditions. Non steroidal hormones for non-lymphoma related conditions are permitted

Any other chemotherapy agent is not allowed.

Traditional herb medicine should not be administered.

Patients are not allowed to receive immunostimulatory medications, including but not limited to IFN $\alpha$ , IFN gamma or IL2.

Patients are not allowed to receive immunosuppressive medications, including but not limited to cyclophosphamide, azathioprine, methotrexate, lenalidomide and thalidomide.

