## **9. STATISTICAL CONSIDERATIONS**

### **9.1 Sample Size Estimation**

Sample size is defined considering CRR as primary study endpoint. Based on the publication by Yamaguchi et al. CRR for newly diagnosed NKTCL with stage III-IV was 40% for regimen of SMILE. Thus, 40% CRR from published study defines null hypothesis (H0) for our trial. The sample size of 20 pts will allow to demonstrate a 30% improvement of CRR from 40% (null hypothesis, H0) with a type 1 error rate=0.05 (two-sided) and power=0.80. Sample size will be 22 under consideration of drop off rate for 2 subjects.

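### Section 7.3 gives intrathecal methotrexate and cytarabine during induction, while Section 7.6 bars methotrexate by name without exception; the two must be reconciled

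*Protocol*

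**What the plan says.** Section 7 of the protocol, on the study intervention, sets out induction (7.1), maintenance (7.2) and then CNS prophylaxis and radiation (7.3). The prophylaxis provision applies to "Patients with involvement of bone marrow, nasal or paranasal sinuses, orbit, breast, kidney, adrenal gland, or testis". It says that these patients "received prophylactic intrathecal methotrexate 10mg and cytarabine 50mg for 4 cycles during induction treatment".

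Section 7.6, on concomitant therapy, contains two bans under its prohibited-medications heading. One is general: "Any other chemotherapy agent is not allowed". The other names drugs: "Patients are not allowed to receive immunosuppressive medications, including but not limited to cyclophosphamide, azathioprine, methotrexate, lenalidomide and thalidomide". The permitted list in the same section covers, for example, infection prophylaxis ("Use of antimicrobial and/or anti viral prophylaxis according to institutional guidelines is allowed"), but intrathecal or CNS prophylaxis is not on it.

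Neither section refers to the other. The regimen in the synopsis and in Section 6.1 is sintilimab plus pegaspargase followed by sintilimab maintenance. Table 3 has administration rows for those two drugs and none for intrathecal treatment.

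**The concern.** Two operative treatment rules in the current text point in opposite directions for the same patients. The intrathecal treatment falls in four of the six induction cycles, before the complete response rate is read at the end of cycle 6.

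Three things are at stake.

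- **Deviations.** It is unclear whether giving the intrathecal drugs, or withholding them, is the departure from protocol.
- **Safety attribution.** Section 8.3 asks the investigator to judge each adverse event against the test drug. Section 7.5 recommends withdrawal after severe chemotherapy toxicity or a chemotherapy delay of more than two weeks. The text does not say whether the intrathecal agents count as chemotherapy for that rule, or as study treatment at all.
- **Description of the regimen.** Results would be reported for a two-drug combination although some patients would also have received two cytotoxic drugs. In a single-arm trial no control group shows what these added, least of all to toxicity.

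**Working it through.** No figure in the plan is at issue, so the check is a comparison of the text, followed by one conditional count.

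**Step 1: methotrexate.** Section 7.3 gives it intrathecally to patients with a listed site. Section 7.6 bars it by name. An exception could sit in any of three places:

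- *In the ban itself.* There is no limit by route or purpose. Exclusion criterion 5, with a similar drug list, confines itself to systemic agents; the ban in 7.6 does not.
- *In the permitted list.* A route exception is written there for inhaled corticosteroids. None is written for intrathecal methotrexate.
- *In the opening paragraph of 7.6.* It allows immunosuppressants after sintilimab has started in order to treat immune-related reactions. CNS prophylaxis is a different purpose.

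No exception is found, so the conflict is direct.

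**Step 2: cytarabine.** It is not named in 7.6. It is caught only by the general ban on other chemotherapy. If 'other' means other than sintilimab and pegaspargase, cytarabine is barred. If it means other than the treatments in Section 7, then 7.3 is part of the baseline and cytarabine is allowed. The text does not settle which.

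**Step 3: how often the trigger is met.** Section 3.1 says that the disease "predominantly occurs in extranodal sites including nasal/paranasal area, and less frequently in skin, gastrointestinal tract and other organs". The nasal and paranasal area is on the 7.3 list, so the trigger is unlikely to be a rarity. Section 3.1 gives no percentage, however, and describes the disease in general, not the stage III-IV patients enrolled here.

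**Step 4: size under an assumption.** The planned number comes from Section 9.1: "Sample size will be 22 under consideration of drop off rate for 2 subjects". With an assumed share *s* of patients having at least one listed site, the expected number under both rules is 22 × *s*:

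| Assumed share | 22 × share | Patients, about |
|---|---|---|
| 25% | 5.5 | 6 |
| 50% | 11.0 | 11 |
| 75% | 16.5 | 17 |
| 90% | 19.8 | 20 |

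The shares are assumptions chosen to span a wide range. None is taken from the protocol.

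**The case against.** The best defence is that the two sections can be read together. Exclusion 5 speaks of systemic immunosuppressives, and the opening of 7.6 speaks of systemic corticosteroids or immunosuppressants and gives interference with sintilimab as the reason. On that view the ban is aimed at systemic immunosuppression, and 7.3, as the specific rule, governs intrathecal use. This may well be what the authors meant, but the ban does not say it. The word 'systemic' appears in exclusion 5 and is absent from the prohibition, which leaves methotrexate barred as written.

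For cytarabine the defence is stronger and largely stands: 7.3 sits in the study intervention section, so 'other' can fairly be read as excluding what that section prescribes.

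Two further points are fair. A synopsis is a summary, and this one also leaves out the radiation provision of 7.3. Table 3 does have rows for concomitant medication and adverse events during induction, so intrathecal doses and their toxicity could be captured. That still leaves open whether they are protocol treatment or a deviation.

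A reader might go further and infer that many, or most, patients cannot be treated within protocol. The documents do not support this. The word 'predominantly' in Section 3.1 yields no proportion for this population, and an investigator who follows 7.3 is following the protocol's own treatment section. Nor do they show that CNS management will differ between investigators; that is a possibility and not a stated fact.

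**Conclusion.** The inconsistency is real and in the current text. It is firm for methotrexate, and conditional for cytarabine on the meaning of 'other'. Section 7.3 is also written in the past tense, so it may be a rule or a description; as a rule it conflicts with 7.6, and as a description it records a drug that 7.6 forbids.

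The number of patients affected is unknown. About 6 to 20 of 22 follows only if the share with a listed site lies between 25% and 90%, which is an assumption.

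The sample size, the definition of the primary endpoint and its analysis are untouched. A reader might also infer that the intrathecal drugs distort the complete response rate. The protocol gives no basis for that: suspected CNS disease is an exclusion, so there should be no known CNS lesion to respond. What is affected is deviation handling, attribution of adverse events and an accurate description of the treatment given.

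**What to change.** 1. Reconcile 7.3 and 7.6 so that one instruction applies to patients with a listed site, covering methotrexate and cytarabine explicitly. Which instruction that is remains a clinical decision for the sponsor.
2. State whether intrathecal treatment counts as protocol treatment or as a deviation, and put 7.3 in the tense of an instruction if it is one.
3. Carry the result into the synopsis and Table 3.
4. If intrathecal treatment stays, write the exception into 7.6, record each administration, and describe the complete response and adverse event results as obtained with that treatment in the patients who had it.

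A comparison of complete response by intrathecal receipt should not be added. Receipt is determined by disease site, so with 22 patients the contrast would be confounded and very imprecise, and it would not resolve the conflict.

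The cost is a short amendment to two sections, a line in the synopsis and one row in Table 3. No extra patients or visits are needed.

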### **7.4 Instructions for Initiation of a New Cycle**

A new course of treatment will begin on the scheduled Day 1 of a new cycle if:

1. ANC >1000 cells /mmc
2. platelet counts > 50.000/mmc
3. irAEs resolved to Grade 0 or 1

### **7.5 Management and monitoring of AEs**

Dose modifications: there will be no dose modifications in this study. Patients with severe chemotherapy toxicity or patients who delay chemotherapy for more than 2 weeks due to adverse events are recommended to withdraw from the study.

Sintilimab treatment may be temporarily suspended in patients experiencing toxicity considered related to study treatment. If corticosteroids are initiated for treatment of the toxicity, the must be tapered over > 1 month to <10 mg/day or oral prednisone or equivalent before sintilimab can be resumed. If sintilimab is withheld for > 12 weeks treatment can be resumed prior approval by the principal investigator. In Table 1 is reported a guideline for the management of patients who experienced specific adverse events (see also Appendix 5).

AEs associated with sintilimab exposure may represent an immunologic etiology. These immune-related AEs (irAEs) may occur shortly after the first dose or several months after the last dose of sintilimab treatment and may affect more than one body system simultaneously. Therefore, early recognition and initiation of treatment is critical to reduce complications. Based on existing clinical study data, most irAEs were reversible and could be managed with interruptions of sintilimab, administration

of corticosteroids and/or other supportive care. For suspected irAEs, ensure adequate evaluation to confirm etiology or exclude other causes. Additional procedures or tests such as bronchoscopy, endoscopy, skin biopsy may be included as part of the evaluation. Based on the severity of irAEs, withhold or permanently discontinue sintilimab and administer corticosteroids. Dose modification and toxicity management guidelines for irAEs associated with sintilimab are provided in Table 1.

